##### Recruitment {15}

To randomize 200 children, the primary recruitment strategy is a direct approach by study personnel to families of children whose births are recorded in birth certificates which are freely available as a public record at Register of Deeds offices at in all four counties. By law, all births in the county must be registered, assuring that our recruitment efforts will identify children from all sex/gender, and racial and ethnic backgrounds. Details from the child’s birth records, including parents’ names and the child’s name and address, are transcribed by study personnel. When the child is aged 2 months, study staff mail a letter to the child’s home address and follow up with door-knock visits. The recruitment strategy is designed to achieve a distribution of demographic characteristics in the study sample mirroring that of the target population of infants in Lenoir County, NC.

The secondary strategy is a pre-enrollment questionnaire that collects contact information of people who express interest in the study prior to their child reaching the enrollment-eligibility age of 2 months. Interested individuals can record their contact information during an interview with study representatives or by completing a questionnaire on paper or online. Traditional recruitment strategies include word of mouth; recruitment flyers placed in health care facilities, community, and welfare organizations; and social media accounts.

### Assignment of interventions: allocation

#### Sequence generation {16a}

Randomization is stratified according to fluoride concentration in the tap water of the child’s primary dwelling:

•< 0.20 mg/L F inclusive of levels below the threshold of measurement

•≥ 0.20 mg/L F

Within each stratum, and within pre-specified blocks, participants are randomized in a 1:1 ratio to either the fluoridated or non-fluoridated study group. The allocation sequence and study group assignment are generated using the “plan” procedure in SAS v9.4 software.

#### Concealment mechanism {16b}

The allocation sequence is stored in a “split-half” segment of the study database that is protected by a password known only to the unmasked data manager and (as backup) the study biostatistician, thereby concealing the allocation sequence to users. Neither the unmasked data manager nor the study biostatistician is involved in the process of randomizing individuals.

#### Implementation {16c}

Study staff implement the allocation sequence using a randomization module of the Data Management System (DMS). After entering data to verify the study participant’s eligibility and stratum for randomization, staff click a button that executes SQL code which allocates the study participant to one study group, and then assigns the record number of the next, unused row of the allocation table along with the study participant’s 3-digit identification code. The DMS generates a verification code that is stored in the randomization table and recorded in the participant’s casebook providing an audit trail to document that the study participant was randomized. In this way, the DMS does not reveal the study participant’s study group assignment nor the allocation sequence to users.

### Assignment of interventions: blinding

#### Who will be blinded {17a}

The study has quadruple masking. Participants, field center staff, investigators, and clinical examiners are masked as to the participants’ study group assignment throughout the data collection period. Only the unmasked data manager (and, as backup, the study statistician) is not masked.

In order to mask participant’s study group, study personnel and participants are made unaware of the contents of 5-gallon bottles of water delivered to dwellings. This is achieved by a masking procedure that assigns a unique, 5-digit serial number at random to each 5-gallon bottle of water after it has been filled from either the New Bern (fluoridated) or North Lenoir (non-fluoridated) public water systems. Masking is achieved in three steps, each performed by a separate study staff person, and each masked bottle is placed at random into a labeled position in racks that can store 768 bottles. Masked bottles from any single public water system are therefore distributed at random among rack positions and the bottles are identifiable to staff only by their 5-digit identifying code.

When new water bottles are requested at monthly Bottle Consumption interviews, staff execute a bottle allocation routine in the DMS. The underlying SAS code retrieves the study participant’s study group assignment and selects from the supply of masked bottles the necessary number of masked bottles that conform with the study participant’s treatment group assignment. Field center staff deliver then the water to the household.

#### Procedure for unblinding if needed {17b}

There are no anticipated circumstances in which an individual study participant will be unmasked. However, the unmasked data manager will generate the report if an oversight board, e.g., the IRB or Data and Safety Monitoring Board (DSMB), requests an unmasked data report during the data collection period.

### Data collection and management

#### Plans for assessment and collection of outcomes {18a}

Dental caries experience will be recorded on five surfaces of each primary tooth, with caries lesions defined at the threshold consistent with macroscopic enamel loss. Five surfaces per tooth will be enumerated in all primary teeth (maximum = 20 teeth per child), yielding a count of affected surfaces that can range from 0 (no dental caries experience) to 100 (worst possible extent of dental caries experience). The examination uses criteria of the International Caries Detection and Assessment System (ICDAS ≥ 3) [18]. A portable dental chair with overhead lighting and compressed air will be used in the home or comparable setting. After a toothbrush prophylaxis, children will be examined in a supine position with the aid of visual magnification. A research assistant will record data using dental charting software.

Training and calibration procedures for dental examinations will be led by [name] (DDS) who is a board-certified pediatric dentist with extensive experience in the conduct of clinical examinations of preschool-age children for dental caries. [name] will work with the study examiner, [name], to review the online training modules available on the ICDAS website. This will be followed by a 2-h session with [name] to review and discuss clinical cases. Clinical training and calibration sessions will take place during a 2-day session at UNC-Chapel Hill. Drs. [name] and [name] will independently examine 20 preschool children ages 3–4 (who are not in the waterBEST study). Findings will be used to calculate inter-examiner agreement statistics (kappa, weighted kappa, percent agreement, and intraclass correlation coefficient) to quantify the examiner’s performance. An inter-examiner kappa score of ≥ 0.65 for binary classification of caries (IDCAS ≥ 3) will indicate that the examiner is calibrated. A repeat training will be held early in year 6, after one half of the examinations have been completed.

#### Plans to promote participant retention and complete follow-up {18b}

Study staff maintain close contact with families. A member of the study team calls families each month to assess their bottled water needs usage and visits their homes alternate months to deliver water bottles. These contacts create opportunities to keep track of changes in household schedule, changes of address, or disruptions to family routine.

When families move permanently out of the county, we will ask for contact information to keep in touch and potentially to conduct a dental examination near the time of the child’s fourth birthday. For such families, and for children whose intervention is discontinued prior to them completing the study, the parent is asked to give permission for the study team to contact the family near the time of the child’s fourth birthday to complete the 4th Birthday Interview.

Study participants are considered lost to follow-up when they cannot be contacted by the study team for the purpose of water bottle delivery and/or interviews or study visits. To minimize such loss, study participants are asked at enrollment to provide names and contact information for up to four third parties who would be willing to speak with the study team about the family’s whereabouts, in the event that the study team has trouble contacting enrolled study participants.

There is no replacement for study participants who are lost to follow-up.

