#### Criteria for discontinuing or modifying allocated interventions {11b}

The PI may discontinue an individual’s intervention if:The enrolled child begins taking fluoride supplements, as reported by the parent during quarterly health checks.The child moves to a primary dwelling where the concentration of fluoride in tap water exceeds 0.60 mg/L F and the parent has expressed a preference that the child drinks tap water.

The PI may withdraw an individual from the study if:A child relocates to a primary dwelling that is more than 30 miles from their address at the time of enrollment.Any adverse event or other medical condition or situation occurs such that continued participation in the study would not be in the best interest of the participant.The participant meets an exclusion criterion (either newly developed or not previously recognized) that precludes further study participation.

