#### Relevant concomitant care permitted or prohibited during the trial {11d}

All parents are encouraged to clean their child’s teeth using toothpaste. To avoid the risk of ingesting too much toothpaste (e.g., accidentally swallowing half a tube of toothpaste), the parent is given information about fluoride intake, including correct use of toothpaste. Regular dental visits are permitted.

The use of fluoride supplements and use of study water to reconstitute infant formula are not permitted because of the risk of excessive fluoride intake and subsequent dental fluorosis. At quarterly health checks, study staff interview parents and ask questions about the child’s use of fluoride supplements and infant formula. If the child begins taking a fluoride supplement, the intervention is discontinued for the duration of supplement usage. For study children being fed infant formula concentrate, waterBEST provides 3-gallon bottles of non-fluoridated water purchased from Le Bleu Central Distributors of Wilson, NC, with instructions that it be used solely for reconstitution of formula.

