#### Provisions for post-trial care {30}

Parents are given a written report of their child’s dental health after the annual dental screening assessment and after the end-of-study dental caries examination. This will include recommendations for dental care, if required.

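### The retention plan does not assure the fourth-birthday dental examination, the only source of the primary endpoint, to children who stop study water or move away

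*Protocol article*

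**What the plan says.** All references are to the protocol article.

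- **Outcomes {12}** defines the primary outcome as dmfs, counted at a dental examination near the fourth birthday. **Sample size {14}** calls that visit the 4th Birthday Dental Caries Examination.
- **Retention {18b}** first deals with families who move permanently out of the county. Their contact details are requested to keep in touch and "potentially to conduct a dental examination near the time of the child’s fourth birthday".
- The next sentence of {18b} widens the group: "For such families, and for children whose intervention is discontinued prior to them completing the study". The permission sought from these parents is to contact the family near the child's "fourth birthday to complete the 4th Birthday Interview". It names no examination.
- **Criteria for discontinuing {11b}** lists two reasons for which the investigator may stop the intervention: starting fluoride supplements, and moving to a home with tap water above 0.60 mg/L F when the parent prefers tap water. It lists separate reasons for withdrawal from the study, among them relocation beyond 30 miles and this one: "The participant meets an exclusion criterion (either newly developed or not previously recognized) that precludes further study participation".
- **Concomitant care {11d}** treats a supplement-related stop as time-limited: "If the child begins taking a fluoride supplement, the intervention is discontinued for the duration of supplement usage".
- **Missing data {20c}** plans exploratory multiple imputation from annual screening and quarterly data, with best-worst and worst-best sensitivity analyses.

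**The concern.** An interview cannot produce a dmfs count. If staff follow {18b} as written, a child who stops study water but still lives in the area is contacted at age four for an interview only, and a child who has moved may or may not be examined. The primary model in {20a} uses only children with an observed dmfs, so these children drop out of it.

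Two things are at stake. The first is precision: the trial was sized so that its one-sided 80% limit would be narrow enough for the go/no-go rules in {14}. The second is bias. Those rules use the point estimate and its upper limit. If children with more caries are more often left unexamined, and more of them are in the control arm, the estimated benefit shrinks and a worthwhile definitive trial could be turned down. One conceivable route is that parents get a written report on the child's "dental health after the annual dental screening assessment", and what they then do may depend on the caries found.

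**Working it through.** **1. Reproducing the planned size.** Inputs from {14}: half-width 1.1, SD 7.8, one-tailed alpha 0.2, probability of reaching the width 0.8. The required n per group is the smallest that satisfies

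P( t(0.8; 2n−2) × s × √(2/n) ≤ 1.1 ) ≥ 0.80.

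This gives n = 79 per group (probability 0.821; 0.816 if conditioned on the interval covering the true difference), so 158 in all, as stated. Allowing for 20% loss, 158 / 0.80 = 197.5, or 198, and the article rounds up to 200. In the other direction, 200 × 0.80 = 160 evaluable. The margin is 160 − 158 = 2 children.

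**2. Effect of further loss on precision.** The article gives no discontinuation or relocation rate, so the loss rates above 20% are assumptions. The probability uses the formula in step 1.

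| Loss | Evaluable | Half-width at SD 7.8 | Probability of half-width ≤ 1.1 |
|---|---|---|---|
| 20% (plan) | 160 | 1.041 | 0.85 |
| 25% | 150 | 1.075 | 0.67 |
| 30% | 140 | 1.113 | 0.44 |
| 35% | 130 | 1.155 | 0.23 |

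Each step of five percentage points is 200 × 0.05 = 10 children.

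**3. Possible bias.** Let qC and qF be the unexamined shares in the control and fluoridated arms, and let D be the excess mean dmfs of unexamined over examined children, taken as equal in both arms. The full-arm mean is the examined mean plus q × D, so the observed difference understates the full-cohort difference by (qC − qF) × D. All inputs here are assumed.

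- Equal shares: 0 × D = 0.
- 10% versus 5%: 0.05 × 1.1 = 0.06 up to 0.05 × 5 = 0.25, which is 5% to 23% of 1.1.
- 15% versus 5%: 0.10 × 1.1 = 0.11 up to 0.10 × 5 = 0.50, which is 10% to 45% of 1.1.

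**4. A severe scenario.** Take 100 children per arm and the control mean implied by {14}, 1.1 / 0.37 = 2.97. Suppose x more control than fluoridated children are lost after caries is found, with mean dmfs 12, about four times the control mean. The control completer mean then falls by x × (12 − 2.97) / (100 − x):

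- x = 3: 0.28 (25% of 1.1)
- x = 5: 0.48 (43%)
- x = 8: 0.78 (71%; control mean kept unrounded)

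**5. The passages side by side.** {12} needs an examination. {18b} names an interview for discontinued children and a potential examination for movers. {11d} implies that a child on supplements stays in the study and may resume water, while {18b} does not distinguish a temporary stop from a permanent one. Neither {11b} nor {11d} says whether outcome collection continues after water is stopped.

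**The case against.** The strongest reply is that the article never says discontinued children go unexamined. {12} defines dmfs for the study participant without regard to intervention status. {20b} mentions a per-protocol population only for additional analyses, which suggests that the primary analysis is not confined to adherent children. The article also condenses a fuller protocol. This stands as a caution: loss of the endpoint is what follows if {18b} is applied as written, and it is not a stated intention. It does not remove the point, because {18b} does address fourth-birthday follow-up for these children and names the interview.

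Three stronger readings are tempting, and the documents do not support them.

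- *All withdrawn and discontinued children get an interview and no examination.* For families leaving the county an examination is foreseen, though not assured. On children withdrawn for other reasons {18b} is silent.
- *Starting supplements is itself a ground for withdrawal from the study.* The supplement exclusions in Table 1 are tied to what the parent reports at the screening visit. {11b} allows withdrawal only where a criterion precludes further participation, and only at the investigator's discretion. {11d} makes the stop last only while supplements are used.
- *Loss will depend on caries and be heavier in the control arm.* The annual report to parents contains recommendations for dental care and does not mention supplements. The relocation reasons have no stated link to caries. Families and field staff are masked, so a difference between arms could arise only through caries itself. This is plausible but not shown.

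The analyses in {20c} also lessen the consequence. They are exploratory, however, and they rest on screening and quarterly data that children who have left may no longer supply.

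**Conclusion.** The point holds in this form: the article does not assure the primary-endpoint examination to children who stop study water or to families who move out of the county, and the sample size leaves a margin of only two children at the planned 20% loss. The loss of precision follows from the plan's own inputs once a loss rate is assumed: 0.85 at 20%, about 0.67 at 25% and about 0.44 at 30%. Bias is possible but cannot be sized from the documents. It is zero if loss and excess caries are equal across arms, up to about 0.5 dmfs in the moderate scenarios, and 0.78 only if eight excess control children with a mean of 12 surfaces are lost. That last figure illustrates a severe case and is not an expectation.

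**What to change.** - In {18b}, replace *4th Birthday Interview* with *4th Birthday Dental Caries Examination and Interview*, and drop *potentially* for families who move. The examination is then sought for every randomised child whose parent still permits it, whatever the intervention status or address, and the child is analysed in the assigned group.
- In {11b}, state that stopping study water does not by itself end outcome collection, and reconcile {11b} and {11d} on this point.
- Leave unchanged the rules on when water is stopped, and the investigator's discretion to withdraw a child in the child's best interest.

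The cost is one amendment and travel for a few extra examinations. {18a} already plans a portable chair and examinations in the home or a comparable setting. There is time to act relative to the article (March 2024): recruitment began in April 2022 at ages two to six months, so a six-month-old screened then was born about October 2021 and turns four about October 2025. An examination not done near the fourth birthday cannot be recovered later.

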#### Data management {19}

Study staff complete paper clinical report forms (CRFs) designed using Teleform software that is also used for scanning and optical recognition of responses. Electronic clinical report forms (eCRFs) are designed using Microsoft Access. The data are stored on an IRB-approved network drive at UNC-CH that is password protected with two-factor authentication required for remote access. CRF-level input edits enforce data entry for mandatory fields and use logic algorithms to implement skip sequences and to verify user decisions (for example, when determining eligibility based on responses to multiple variables). Data quality is ensured through the data collection system’s continuous monitoring of data and real-time detection and correction of errors. All elements of data entry (i.e., time, date, verbatim text, and the name of the person performing the data entry) are recorded in an electronic audit trail to allow all changes in the database to be monitored and maintained in accordance with applicable regulations.

Data collection and accurate documentation are the responsibility of the study staff under the supervision of the PI. All source documents and laboratory reports will be reviewed by the study team and data entry staff, who will ensure that they are accurate and complete. Unanticipated problems and adverse events must be reviewed by the PI or a designee.

The DMS generates study progress reports (i.e., screening, enrollment, cohort retention, and study progress reports) to the study website periodically throughout the study period, as determined by the NIDCR program official and the PI. The study team will provide monthly enrollment/retention reports to NIDCR for review. The DMS also generates management reports that contain measures of data quality, such as the number of outstanding data queries and data completion rates. Study reports are provided to the DSMB and IRBs prior to their periodic meetings. No interim statistical analyses are planned.


#### Confidentiality {27}

Personal information about potential and enrolled participants is strictly held in trust by the investigators, study staff, and the study sponsor(s) and their agents. This confidentiality is extended to cover the testing of biological samples in addition to any study information relating to participants. No information concerning the study or the data will be released to any unauthorized third party without prior written approval of the study sponsor.

The study monitor or other authorized representatives of NIDCR may inspect all study documents and records required to be maintained by the investigator, including but not limited to, medical records (office, clinic, or hospital) for the study participants. The clinical study site will permit access to such records.

#### *Plans for collection, laboratory evaluation, and storage of biological specimens for genetic or molecular analysis in this trial/future use {33***}**

Laboratory processes involved in measuring fluoride in fingernail and toenail clippings destroy the original material, rendering the nail clippings unable to be used for identification.

### Statistical methods

#### Statistical methods for primary and secondary outcomes {20a}

The statistical analysis for the primary objective will estimate efficacy and the one-tailed, upper 80% confidence limit of the estimate. Efficacy is defined as the estimated difference in adjusted mean dmfs per child between intervention groups, calculated with a general linear model estimated by ordinary least squares using the SAS “GLM” procedure. The dependent variable will be the child’s dmfs index, an integer (count) measure with a potential range of 0–100 surfaces. The main predictor variable will be the study group (modeled as a binary, dummy variable) and covariates will be randomization stratum (modeled as a binary, dummy variable) and child’s age, in months, at the time of the examination (modeled as a continuous variable). An “estimate” statement in the GLM procedure will calculate the adjusted mean and 1-tailed, upper 80% confidence limit.

